#### 3. Neurovascular measures

##### a) Whole-brain functional MRI studies

We have previously used functional Magnetic Resonance Imaging (fMRI) to localise the motor cortex in patients with tumours and dysplastic lesions[44], to monitor the sensory cortex in patients recovering from stroke[45,46] and to examine functional reorganisation in cerebral palsy[46,47] and have combined this with TMS to localise the motor cortex in stroke patients[48]. We now plan to use similar techniques to investigate brain reorganisation in response to therapy in children with CP. Brain reorganisation has been demonstrated using TMS and fMRI following intensive UL training in adults after chronic stroke[49]. Functional MRI or blood oxygen level dependent (BOLD) contrast is a robust and non-invasive method of detection of regional tissue changes in venous oxygenation in response to task related activation[50].

Functional MRI has provided new information in understanding real time cerebral blood flow changes in response to behavioural activation[51]. Recent fMRI studies have shown that individuals with chronic stroke can be trained to improve finger control with intensive practice and this can be accompanied by increases in motor cortex activation[49]. It has been suggested that intensive arm training may result in rapid brain reorganisation[52]. Our group has undertaken the first study of serial fMRI in young children with CP to determine central neurovascular responses to treatment[33]. We have achieved 90% compliance with serial fMRI and good reproducibility of the location of activation for the unimpaired limb for two motor tasks in children with hemiplegia. There are a very limited number of motor studies with fMRI in children with CP and no serial fMRI motor studies measuring outcome associated with intense models of UL training.

Functional imaging at 3 tesla on a Siemens MAGNETOM Trio MR scanner will be conducted at the Brain Research Institute, Melbourne. This research dedicated 3T scanner provides approximately twice the signal to noise ratio for functional imaging compared to conventional 1.5 tesla scanners. We take advantage of this to reduce the time in the scanner for children and improve the resolution of data collected. To prepare for the real fMRI scan all children will practice in a mock MRI scanner using techniques that have achieved 90% compliance in our earlier studies. During scanning of their anatomical images the children will be able to watch a favourite video. Children will lie supine, with their head immobilised with one immobilisation pad to minimise head movement. In the scanner, children will perform two motor tasks, active and passive wrist extension at 2 Hz. These tasks are frequently impaired in children with hemiplegia and most likely to show a response to training. Individual forearm resting splints will standardise the starting positions. The motor paradigm will consist of a 2-condition block design, visually cued via instructions projected on a screen. The baseline condition is no movement. A tape recording of a metronome at 2 Hz will provide an auditory cue for the rate of movement. Verbal cues to commence and end the task will be given. The task and rest periods are 30 seconds with the activation cycle repeated four times. An additional five minutes of resting-state fMRI will also be collected for analysis of functional connectivity. Tasks performed prior to resting-state fMRI can influence functional connectivity[53], so the resting-state data will be collected after the motor paradigms have been completed to provide some consistency in this regard. The whole assessment will take no longer than 45 minutes. The actual movements performed in the scanner will be rated for speed, the range of motion actually performed, ability to isolate the movement and presence of mirror movements in the contralateral hand or general body movements. If there is evidence of task-correlated breath-holding[54], the task will be repeated.

Functional MRI will be acquired using a BOLD acquisition sequence (Gradient-recalled-echo (GRE) echo-planar imaging (EPI), Repetition Time (TR) = 3.0 s, Echo Time (TE) = 30 ms, Flip angle = 85°, Slice thickness = 3 mm, FOV = 216 mm, 44 slices, 72 × 72 matrix yielding an in-plane resolution of 3.0 mm × 3.0 mm). A single set of T2-weighted anatomical, FLAIR and 3D T1 volumes will also be collected. Functional MRI image processing, analysis and visualisation will be performed using iBrain(tm) software[46] and SPM software (Wellcome Department of Imaging Neuroscience, London, UK).

Pre-processing of the fMRI images will include slice-timing correction using a temporal interpolation scheme to estimate the response at the time of commencement of each acquisition volume, motion correction (realignment) within session and nonlinear registration across sessions for each participant, and spatial normalisation to the standard Montreal Neurological Institute (MNI) template supplied with SPM. In the realignment step, images within a session will be aligned to a single target image within that time series to minimise the effects of participant motion between scans. The target selected by iBrain(tm) is the image whose within-brain centre-of-mass is located closest to the median of all images in that time series. Target images from each session of a subject will then be non-linearly spatially normalised to a subject-specific space in an iterative fashion to ensure unbiased registration of images across sessions; this step is designed to correct, as far as practicable, non-linear image distortions that may differ from session to session. The step will be undertaken within subject rather than directly to the standard template to maximise the fidelity of within-subject registration. The mean of the within subject registered images will then be spatially normalised to the standard MNI template. Because many participants have large lesions, spatial normalisation to the MNI template will be undertaken using only an affine transform. In practice, the image transformations derived in each step described above will first be combined and then applied in one step to minimise resampling artefact when writing the final images. The spatially normalised image data will be smoothed with an isotropic Gaussian kernel at least twice the voxel size to fulfil the assumptions of Gaussian random field theory (RFT).

Using the general linear model (GLM), statistical parametric maps will be computed for each session of each subject. Temporal autocorrelation will be modelled using a white noise and autoregressive AR(1) model within SPM. Motion correction parameters will be included as covariates of no interest. Details regarding the specific implementation of the GLM and RFT by SPM are available elsewhere[55]. Due to the heterogeneity in lesion location and size across participants, group analysis of intra-participant change in activation will be undertaken using a region of interest approach with the assistance of iBrain(tm) software.

##### b) Diffusion Imaging Acquisition and White Matter Fibre Tracking

Participants will be scanned using a 3T Seimens MAGNETOM Trio whole body MRI scanner located at the Brain Research Institute, Melbourne. In addition to a number of standard radiological scans (T1, T2, FLAIR and 1 mm isotropic MPRAGE structural scan), diffusion-weighted images suitable for tractography studies will be acquired using a fully optimised single-shot, spin-echo echo-planar diffusion sequence. The imaging parameters will be (54 axial slices, TR/TE 7200/110 ms, 2.3 mm isotropic resolution, acquisition matrix: 104 × 104, parallel imaging reduction factor of 2, 60 diffusion encoding directions with a *b *value of 3000 s mm^-2^). The total imaging time for this sequence is 9 minutes. Diffusion-weighted MR white-matter tractography will be undertaken in a manner robust to crossing fibres, using constrained spherical deconvolution (CSD) and probabilistic streamlines[56-58] using MRtrix software (Brain Research Institute, Melbourne Australia; http://www.brain.org.au/software).

##### c) Brain Reorganisation

Transcranial Magnetic Stimulation (TMS) will be performed on all participants in both groups at baseline then at 3 and 26 weeks post intervention. TMS will be delivered to both hemispheres. For each participant, care will be taken to perform both studies at approximately the same time of day so as to increase the repeatability of the measurements.

During TMS, participants will sit in a comfortable, reclining chair. Surface electromyographic (EMG) recording will be made from the abductor pollicis brevis muscle (APB) using disc electrodes in a tendon-belly arrangement. The motor evoked potentials (MEPs) will be recorded on an Oxford Medelec Synergy electromyography machine. Band-pass filtering (10 - 5000 Hz) was used. Sweep speed for threshold determination will be 100 ms and the gain will be set to 100 μV/div. Auditory EMG feedback will be given to ensure complete, voluntary relaxation of the target muscles.

The experimental session will record the following parameters:

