## Methods/Design

A matched pairs randomised trial will be conducted using an activity based day camp model[30] to evaluate the efficacy of CIMT compared to BIM training in children with congenital hemiplegia aged 5 to 16 years.

The specific hypotheses to be tested are:-

1. CIMT will reduce activity limitations and participation restrictions to a greater extent than BIM training in children with hemiplegia.

2. CIMT will result in greater use-dependent brain reorganisation compared to BIM training and this cortical plasticity will be retained for longer periods.

3. CIMT will result in greater enhancement of participation in school and community roles.

4. CIMT will result in greater improvements in QOL.

These hypotheses will address the following specific aims:-

1. Upper limb rehabilitation consumes a great deal of time and is costly, and the effects may be short lived. CIMT is a novel upper limb training where the unimpaired arm is constrained in a "glove like splint" while the impaired hemiplegic arm is intensively trained. This study will determine which training approach has the greatest impact on activity limitations and how long that effect is retained.

2. If one approach results in greater enhancement and retention of cortical reorganisation then this will guide clinical practice with implications for other patients (Traumatic Brain Injury TBI, stroke). An understanding of the nature and timing of the brain lesion may indicate which children respond better.

3. If a training program enhances community participation and improves QOL this will have a profound impact on educational opportunities and vocational roles.

Assessments will be performed at baseline prior to the camp and then at three weeks following completion of the camp. Further follow-up will be performed at 26 and 52 weeks following intervention to determine retention of effects. The experimental design and outcome measures are depicted in Figure 1.

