### Inclusion criteria

The study will include children and youth:

1. With a confirmed diagnosis of congenital hemiplegia.

2. Aged 5 to 16 years.

3. With predominant spasticity rather than dystonia interfering with UL function according to the classification of motor type by Sanger et al[31] with Modified Ashworth Scale (MAS) grade >1 but <3[32].

4. Ability to achieve minimal active grasp with the impaired hand.

5. Sufficient co-operation and cognitive understanding to participate in the group activities.

For a subset of children performing the Advanced Brain Imaging and Transcranial Magnetic Stimulation (TMS) studies further inclusion criteria are:-

1. Sufficient co-operation to perform Advanced Brain Imaging studies for 45 minutes.

2. No exclusions for 3 tesla Magnetic Resonance Imaging (3T MRI) including no metal implants, no shunts, no uncontrolled epilepsy as the later would be a confound.

3. For TMS there must be no current or previous history of epilepsy.

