### Analyses

All assessment forms will be developed using scannable Teleforms (Teleform, 2005). Forms will be entered, scanned and visually checked by staff trained in use of the software. Data will be transferred electronically into Microsoft Access 1997. Analyses will be on an intention-to-treat basis using STATA 10. Data from each outcome measure will be summarised for each treatment group and descriptive statistics (frequencies, means, medians, 95% confidence intervals) calculated dependent on data distribution. We anticipate that groups will be similar on baseline measures due to the matched pairs design. Initially between group differences will be evaluated at the three follow-up assessment points using independent t-tests or Wilcoxon rank sum test. Within group changes between baseline and the follow-up assessments for continuous variables will be evaluated using paired t-tests or Wilcoxon matched-pairs sign rank test. A significance level of 0.05 will be used.

For the TMS data Student's paired t-test will be used for analysis of the difference between pre and each post intervention (3 and 26 weeks) mean MT and MEP ratios. This will be performed in each group for the impaired side and the unimpaired side.

To determine the intra-rater reliability of our trained occupational therapist rater on the MUUL, intraclass correlation coefficients will be calculated (3.1) with 95% confidence intervals from total MUUL percentage scores[101]. The standard error of measurement (SEM = SD × √(1-ICC)) and the smallest detectible difference (SDD = SEM × 1.96 × √2) will be calculated[102].

Post hoc analyses will be undertaken to investigate clinical characteristics of children who have a greater response to either intervention.

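### The TMS analysis paragraph names only within-arm paired t-tests, which cannot test the between-arm hypothesis on brain reorganisation; a baseline-adjusted arm comparison should be stated

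*Protocol article*

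**What the plan says.** Methods/Design lists as hypothesis 2: "CIMT will result in greater use-dependent brain reorganisation compared to BIM training and this cortical plasticity will be retained for longer periods".

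On who has TMS and when, section c) Brain Reorganisation states: "Transcranial Magnetic Stimulation (TMS) will be performed on all participants in both groups at baseline then at 3 and 26 weeks post intervention". Inclusion criteria is narrower. It introduces extra conditions with "For a subset of children performing the Advanced Brain Imaging and Transcranial Magnetic Stimulation (TMS) studies further inclusion criteria are" and then adds "For TMS there must be no current or previous history of epilepsy".

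On analysis, the Analyses section has two relevant parts.

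- A general part, written for the outcome measures as a whole: "Initially between group differences will be evaluated at the three follow-up assessment points using independent t-tests or Wilcoxon rank sum test". It is preceded by the remark "We anticipate that groups will be similar on baseline measures due to the matched pairs design" and followed by paired within-group tests.
- A separate TMS paragraph, covering motor threshold and MEP ratios at 3 and 26 weeks: "paired t-test will be used for analysis of the difference between pre and each post intervention". It continues: "This will be performed in each group for the impaired side and the unimpaired side".

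**The concern.** Hypothesis 2 says that one arm changes more than the other. A paired t-test within an arm has a different null hypothesis, namely that the mean change in that arm is zero. Running it in each arm and setting the two p-values side by side does not test whether the changes differ. A p-value just below 0.05 in one arm and just above it in the other is compatible with identical true changes.

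What is at stake is the reading of a named secondary hypothesis. If the TMS paragraph is followed as written, the report will hold many within-arm p-values and no estimate of the arm difference. A significant change in the CIMT arm alone could then be taken as support for hypothesis 2. The baseline TMS values, which would sharpen a direct comparison, would serve only the within-arm tests.

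There is also a small wording conflict. The Brain Reorganisation section speaks of every participant, whereas Inclusion criteria confines TMS to children with no history of epilepsy. The trial's general inclusion and exclusion criteria do not bar such a history.

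**Working it through.** **Plan's own figures.** The plan gives no effect size, SD, power or subset size for TMS, so there is no TMS figure to reproduce. Its one sample-size figure is for the MUUL: difference 7, SD 9, alpha 0.05 (two-sided assumed), power 80%. The normal approximation gives 2 × (1.960 + 0.842)² × 9² / 7² = 25.9, rounded up to 26 per group, as stated. Nothing below alters it.

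**Step 1: match hypothesis to test.**

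| Item | Where | What it addresses |
|---|---|---|
| Hypothesis 2 | Methods/Design | CIMT change minus BIM change, and how long it lasts |
| TMS paragraph | Analyses | Change from baseline within CIMT, and separately within BIM |
| General between-group sentence | Analyses | Arm difference at three follow-ups; TMS not named; no baseline adjustment stated |

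TMS is measured at two follow-ups (3 and 26 weeks), not three. The general sentence therefore fits TMS only if read as applying wherever a measure is taken.

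**Step 2: count the tests in the TMS paragraph.** 2 measures (motor threshold, MEP ratio) × 2 follow-ups × 2 sides × 2 arms = 16 within-arm tests. If each of the four stimulus intensities in the recruitment-curve section were tested separately, the count would be (1 + 4) × 2 × 2 × 2 = 40. The plan does not say which applies. Between-arm tests named in that paragraph: 0.

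**Step 3: how often a split result arises with no arm difference.** Let both arms have the same true change, and let p be the power of the paired test in each arm (assumed; not in the plan). The arms are independent, so

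P(exactly one arm significant) = 2p(1 − p).

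- p = 0.2: 2 × 0.2 × 0.8 = 0.32
- p = 0.5: 2 × 0.5 × 0.5 = 0.50
- p = 0.8: 2 × 0.8 × 0.2 = 0.32

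A simulation with 26 per arm and a common true change of 0.4 SD gave per-arm power 0.50, exactly one arm significant in 0.50 of runs, and a direct between-arm t-test significant in 0.050. A second simulation used 13, 18 or 26 per arm and common changes of 0, 0.3 or 0.5 SD. It gave split results in about 9% (no change in either arm) to 50% of runs.

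**Step 4: what baseline adjustment would add if the general sentence does cover TMS.** Let r be the baseline-to-follow-up correlation (assumed; not in the plan). The variance of the arm difference, relative to an unadjusted follow-up comparison, is:

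| r | ANCOVA, 1 − r² | Change score, 2(1 − r) |
|---|---|---|
| 0.5 | 0.75 | 1.00 |
| 0.7 | 0.51 | 0.60 |

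ANCOVA is the more precise of the two at either value.

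**The case against.** The strongest reply is that a between-arm test for TMS is already in the plan. The general part of Analyses speaks of every outcome measure, and the abstract lists TMS among the outcomes. On that view the TMS paragraph only supplements the general text, much as the within-group sentence does for other measures, and the mismatch of three follow-ups against two is trivial. This is a fair reading, and a reader who inferred that the protocol has no between-arm TMS test at all would go too far. What stands is narrower: the only text naming TMS gives a test that does not answer the hypothesis, and the general sentence, if it applies, states no use of baseline. Sample size does plan on changes, but for the MUUL, and Analyses does not carry that over to TMS.

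An unadjusted comparison of randomised arms is also valid. That is correct; adjustment buys precision rather than removing bias.

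A reader might further infer that the TMS analysis population is undefined, or that a safety rule is missing. Neither follows. Inclusion criteria states who is eligible and, as the specific rule, governs the looser procedures text. Nor do pairs with one TMS-ineligible child bias the comparison: epilepsy history at entry precedes randomisation, and the stated between-group tests do not use the pairing.

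Finally, hypothesis 2 does not rest on TMS alone, since fMRI also addresses brain reorganisation, and nothing in the plan says that significance in one arm only will be treated as an arm difference. Both points limit the stakes.

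**Conclusion.** The point holds in a limited form. Hypothesis 2 is a between-arm claim, and the TMS paragraph names only within-arm tests, which cannot test it. Depending on whether the general sentence is meant to cover TMS, the hypothesis gets either no between-arm TMS test or one that, as worded, leaves the baseline TMS values unused.

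The 32% to 50% is illustrative. It depends on an assumed per-arm power of 0.2 to 0.8 and on someone reading one-arm significance as an arm difference; it is not a predicted error rate for this trial. The precision gain likewise depends on an assumed correlation. The plan gives no epilepsy rate, so the number of children with TMS data cannot be stated.

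TMS is a secondary measure. The primary MUUL comparison and the total of 52 children are untouched. The conflict over who receives TMS is a wording slip.

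**What to change.** In Analyses, add one sentence to the TMS paragraph: for TMS, hypothesis 2 is tested by comparing the arms on the 3-week and 26-week motor threshold and MEP values, each adjusted for its baseline value by ANCOVA, among children eligible for TMS under Inclusion criteria. Report the adjusted difference with its 95% confidence interval. Keep the within-arm paired t-tests and label them descriptive.

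In section c) Brain Reorganisation, qualify the reference to participants with the words 'who meet the TMS criteria', so that it agrees with Inclusion criteria.

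The cost is one sentence and one clause. All the data needed are already collected at baseline, 3 and 26 weeks. TMS conclusions will apply only to children without a history of epilepsy, which the eligibility rule already implies.

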###### i) Motor Threshold (MT)

Stimulation will commence at 30% of maximum output and increase in 5% increments until the motor evoked potential (MEP) is established. 1% changes in intensity will then used to calculate the threshold value. Motor threshold is defined as the lowest level of stimulus intensity which produced a MEP in the target muscle of peak-to-peak amplitude > 100 μV on 50% or more of 10 trials[59].

###### (ii) MEP Recruitment Curves

The maximum compound muscle action potential (CMAP) amplitude of the resting APB will be determined by supramaximal stimulation of the median nerve at the wrist. For each participant, the average of the CMAP amplitudes obtained after three stimuli will be calculated as was defined as 100%[60]. MEPs obtained by Single pulse TMS using different randomized stimulus intensities of 110, 120, 130, and 140% MT will be expressed as a percentage of the CMAP in order to obtain recruitment curves[61]. An average of 10 peak-to-peak MEPs recorded for each stimulus intensity will be calculated.

For motor thresholds and recruitment curve measurements, the stimulus will be delivered to the contralateral cerebral hemisphere using the appropriate direction of coil current flow (anticlockwise for left cortical stimulation and clockwise for right cortical stimulation). This will be performed using a flat circular 9 cm diameter magnetic coil (14 cm external diameter) connected to a Magstim stimulator (Magstim, Whitland, Dyfed, United Kingdom). The centre of the coil will be positioned over the vertex and held in a plane tangential to it. The coil will be held in place by a support stand, and its position will be checked regularly through each experiment.

